**Figure 2. f2:**
[figure not shown]
Northumbria Healthcare NHS Foundation Trust anaemia pathway demonstrating haemoglobin threshold values used to determine treatment
^17^.

Treatment options from the pathway (
Figure 2) include iron (oral or IV) or referral for further investigation (to GP or haematologist) prior to surgery. This means it may be possible to examine the effects of the anaemia screening policy for all anaemic patients (including all treatments), but also to isolate the effects of treatment with iron by excluding patients who do not qualify for iron treatment (as per the pathway in
Figure 2). Data permitting these variations will be explored. 

***Addressing threats to validity.*** Manipulation of treatment status by patients through manipulation of the assignment variable (Hb concentration) is highly unlikely. However, it is possible the reporting of the assignment variable could be manipulated by clinicians, although there is a protocol which healthcare professionals are required to, and report they, strictly adhere to. Nonetheless, steps will be taken to assess the internal validity of the data. A plot of assignment variable (Hb) against probability of receiving treatment will be created to inform if a sharp or fuzzy design is most appropriate
^29^. A histogram of the assignment variable (Hb) data will be visually inspected for bunching around the threshold values. This will also be tested using the McCrary density test
^32^. To test if groups either side of the threshold are comparable, summary statistics of non-outcome variables will be presented for those who fall just either side of the threshold. Formal testing (such as t-test for continuous variables) will be undertaken to assess for any statistically significant differences between groups either side of the threshold. It is predicated that some non-outcome variables such as age or comorbidities may affect outcome. As such sensitivity analyses incorporating these as covariates are planned regardless of the comparability of the two groups. If no differences between groups either side of the threshold are seen, this supports the assumption that assignment around the threshold is random and supports that there has been no manipulation of treatment status, similar to a RCT
^28^. If differences are seen, and it is possible the more anaemic patients (lower Hb) have more comorbidities and/or are older, then variables which are identified as being different between the two groups will be included as covariates in the final model. Similar to ITS, RDD is sensitive to co-interventions introduced around the threshold Hb value. There are no known co-interventions introduced locally for this patient cohort around the threshold Hb values.

***Developing the model.*** In graphical representations of the data, Hb will be divided into bins. Outcome data for this study is in the form of discrete variables (yes/no: transfused / readmitted / critical care admission; and number of inpatient days). As such, outcome data will be converted to a probability (i.e. risk of transfusion) or average (i.e. mean number of days) for each bin. To decide optimal bin size, plots of Hb and primary outcome (transfusion rate) will be generated for a range of bin sizes (i.e. 1, 2 or 5 g/L). Visual inspection of these plots will be used to rule out bin sizes that are clearly too wide or too narrow. For the remaining bin sizes, F-tests using
*k*2 dummies and interactions will be performed to identify bin sizes that do not over smooth the data. From the remaining choices the widest bin size that is not rejected by either F-test will be chosen
^32^. The same bin size as chosen for the primary outcome will be used for plotting other outcomes to facilitate comparison. 95% confidence intervals will be plotted alongside the probabilities or averages where applicable.

Separate scatter plots of primary and secondary outcomes against Hb will be created. These will be inspected visually for a jump at the threshold value, indicative of a treatment effect. Data will be inspected for outlying data points and consideration given to exclusion. Sensitivity analysis with and without outlying data points will be performed.

As the sample size for this analysis is relatively small a parametric estimation of treatment effect will be used for the primary analysis using logistic regression
^32^. Length of stay will be considered as a continuous outcome. The F-test will be used to determine the optimal functional form of the parametric regression model. Starting with a simple linear model, a higher order term will be added to the model until the F-test is no longer statistically significant
^32^.

For the dichotomous outcomes of transfusion, readmission and readmission to critical care, logistic regression will be used. In all analyses, the simplest valid model will be preferred. Robustness checks of the models in which the outermost 1, 5 and 10% of data points are dropped will be conducted.

A nonparametric (local linear regression) approach will be taken in sensitivity analyses, within which the bandwidth will be determined by the cross-validation method
^32^. Further analyses with data stratified by surgery type (THR or TKR) will be conducted where data permits.

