http://www.R-project.org/) on an intention to treat basis, and per protocol where possible. Results will be presented in terms of absolute and relative values with 95% confidence intervals where appropriate. Results will be considered statistically significant if the p-value ≤0.05.

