### Regression discontinuity

RDD estimates the local average treatment effect when treatment decisions are based around a cut-off value for a continuous variable
^26^. For example, giving iron (the treatment) with the intention of reducing RBC transfusion and LoS (the outcomes) to patients whose Hb (the assignment variable) falls below a pre-defined cut-off of 120g/L for females or 130 g/L for males (the threshold). RDD makes use of this threshold and assumes that individuals who lie just above it belong to the same populations those who lie just below it, and assignment to treatment or not is considered random
^27^.

The main strength of RDD lies in its ability to achieve a balance of unobserved factors in patients that fall, by chance, either side of the threshold value, much like a RCT
^28^. The local nature of the effect examined in RDD can also be used in optimising threshold levels. In this case we may be able to examine if a threshold Hb of 120 or 130g/L may be more appropriate for females, as is being suggested in some studies
^12,
28–
30^. As the TXA policy affects all patients it is only possible to conduct a RDD analysis for the anaemia screening programme, using data since the inception of this programme (1
^st^ February 2013,
Figure 1).

***Data description.*** In this study the continuous assignment variable will be preoperative Hb concentration. The outcome assessment, for primary and secondary outcomes (listed above), are observed universally for patients who receive treatment or not. Details of how treatment is assigned has been previously reported, and is shown in
Figure 2
^17^. Notably the treatment thresholds are different for males (Hb 130g/L) and females (120g/L), so data will be stratified by gender for analysis. The treatment thresholds are based on World Health Organisation definitions for anaemia
^31^.

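### The regression discontinuity balance check compares raw group means with no haemoglobin term and no stated window, so it cannot tell a smooth covariate gradient from a jump at the threshold, yet it selects covariates for the final model

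*SAP article*

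**What the plan says.** The check is in the SAP article under Regression discontinuity, Addressing threats to validity.

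- Descriptive step: "summary statistics of non-outcome variables will be presented for those who fall just either side of the threshold". The width in g/L is not given.
- Test: "Formal testing (such as t-test for continuous variables) will be undertaken to assess for any statistically significant differences between groups" on the two sides. The general significance rule, under Data source, is "Results will be considered statistically significant if the p-value ≤0.05".
- Reading of a null result: "If no differences between groups either side of the threshold are seen, this supports the assumption that assignment around the threshold is random". The same sentence takes it as support for no manipulation of treatment status.
- Reading of a positive result: the SAP remarks that "it is possible the more anaemic patients (lower Hb) have more comorbidities and/or are older", and then says that "variables which are identified as being different between the two groups will be included as covariates in the final model".
- Safeguards: a histogram of Hb, a McCrary density test, and, for variables such as age and comorbidities, "sensitivity analyses incorporating these as covariates are planned regardless of the comparability of the two groups".

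The analysis is split by sex: "Notably the treatment thresholds are different for males (Hb 130g/L) and females (120g/L), so data will be stratified by gender for analysis". Under Developing the model, the primary RDD estimate is parametric (logistic regression for the binary outcomes). A cross-validated bandwidth appears only in the nonparametric sensitivity analysis.

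**The concern.** The design rests on baseline characteristics being continuous in Hb at the cut-off. They may slope with Hb on either side without harming the estimate, because Hb is in the outcome model. A t-test asks whether the mean over some window below the threshold equals the mean over some window above it. If age falls smoothly as Hb rises, those means differ in a perfectly valid design, and the gap grows with the window. The reverse also holds: a real jump that runs against the gradient can be hidden.

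The result is used twice. It is evidence on random assignment at the threshold, and it decides which covariates enter the final model. Because strata are analysed separately, selection by significance could leave women and men with different adjustment sets. In a logistic model, adding prognostic covariates also changes the conditional odds ratio being estimated. A SAP published before analysis is meant to remove such choices.

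**Working it through.** The SAP gives no window, sample size or error rate for this check, so there is no stated figure to reproduce. The calculation asks how often a two-sided 5% raw comparison rejects when age is smooth in Hb and there is no jump.

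**Inputs from the SAP article.** 20,772 procedures from January 2008 to March 2019 (135 months); RDD data from 1 February 2013 (74 months); female threshold 120 g/L; significance at 0.05 (two-sidedness assumed).

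**Assumed inputs.** Accrual pro rata, 20,772 × 74/135 ≈ 11,386; 55% female, 11,386 × 0.55 ≈ 6,260; Hb in women normal with mean 132 and SD 12 g/L; age SD 10 years; age gradient b = 0.05, 0.1 or 0.2 years per g/L.

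**Formula.** With n₁ and n₂ patients in the window below and above 120, and G the gap between their mean Hb values:

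- expected age difference d = b × G
- SE = 10 × √(1/n₁ + 1/n₂)
- rejection rate = Φ(d/SE − 1.96) + Φ(−d/SE − 1.96)

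**Worked cases.**

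- ±2 g/L, b = 0.1: n₁ = 232, n₂ = 273, G = 2.0, d = 0.20, SE = 0.89, d/SE = 0.22, rejection about 6%.
- ±5 g/L, b = 0.2: n₁ = 503, n₂ = 759, G = 4.9, d = 0.99, SE = 0.57, d/SE = 1.72, rejection about 40%.
- ±10 g/L, b = 0.1: n₁ = 784, n₂ = 1,723, G = 9.5, d = 0.95, SE = 0.43, d/SE = 2.20, rejection about 59%.

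**Simulation with whole-number Hb (2,000 runs, Welch t-test).** The jump test regresses age on a below-threshold indicator, Hb, and their interaction in the same window.

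| Window (g/L) | Raw test, b = 0.05 | b = 0.1 | b = 0.2 | Jump test, b = 0 to 0.2 |
|---|---|---|---|---|
| ±2 | 5% | 6% | 8% | not run (too few distinct Hb values) |
| ±5 | 6% | 13% | 40% | about 5% |
| ±10 | 19% | 58% | 99% | 4–5% |
| ±20 | 61% | 99% | 100% | 4–5% |
| all data | 88% | 100% | 100% | 4–5% |

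With b = 0 the raw test rejects in about 5% at every window, so the excess comes from the gradient alone.

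**Range over sample size and gradient.** A second simulation took 3,000 to 6,000 women and age–Hb correlations of 0.1 to 0.3 in size. With SDs of 10 and 12 these are gradients of 0.1 × 10/12 = 0.08 to 0.3 × 10/12 = 0.25 years per g/L. The raw test rejected in about 5–9% at ±1 to 2 g/L, 6–52% at ±5 and 23–100% at ±10. The jump test rejected in about 3–6% at ±5 and ±10.

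**Power in a narrow window.** At ±2 g/L, SE = 0.89 years. For a true 2-year difference, 2/0.89 = 2.24, which gives power of about 60%. For 1 year it is about 20%. Narrowing the window removes the false alarms but leaves a null result weakly informative.

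**Price of the jump test.** For Hb roughly uniform over width h on one side, the fitted value at the boundary has variance (σ²/n) × [1 + (h/2)²/(h²/12)] = 4σ²/n, against σ²/n for a mean. Simulated variance ratios were 3.6 to 4.4. For a true 2-year jump with no gradient and 6,000 women, power at ±5 g/L is about 33–37% for the jump test and 88–90% for the raw test. At ±10 g/L it is 64% and 99%.

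**The case against.** The strongest reply is that the SAP never uses the test as a pass or fail rule. A reader might infer that a significant t-test would lead to a valid design being reported as failing its key assumption. The text does not support that: it interprets only the null result as evidence on assignment, and its response to a difference is adjustment. It even names the gradient as a possible explanation, and only as a possibility. This part of the objection stands in full.

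Next, the descriptive step concerns patients just either side of the threshold, and the section Comparing ITS and RDD illustrates similarity with women at 119 and 121 g/L. In windows that narrow the false-alarm rate is close to nominal, so it would be wrong to say that the test misleads in every window. That stands too. But no width is fixed, the sentence on formal testing does not repeat the restriction, and the primary model is not confined to a narrow band from which a width could be borrowed.

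Third, the McCrary test and the covariate-adjusted sensitivity analyses mitigate the problem. They do so only in part. McCrary examines the density of Hb, not covariates, and the sensitivity analyses do not stop the raw test from choosing the final model. Adding a covariate that is smooth in Hb should do little harm to the threshold estimate, and no bias in it has been shown.

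The wording also offers the t-test only as an example, in a condensed article. That leaves the choice of test open, but what is described is still a comparison of groups rather than a test for a jump.

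Finally, the jump test is the less powerful of the two in a given window. That is a real cost of the remedy.

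**Conclusion.** The point holds, with limited harm. The named test does not condition on Hb, its window is open, and its result both counts as evidence on assignment and selects covariates. Under the assumptions shown, false alarms are near nominal at ±1 to 2 g/L, about 6–52% at ±5 and 23–100% at ±10 g/L. These sizes depend on the assumed sample, Hb distribution and gradient, none of which the SAP gives. The direction does not: any smooth gradient inflates the raw test, and more so as the window widens. What is at stake is a misleading balance check and a significance-driven adjustment set. It is not a design declared invalid, nor a demonstrated bias in the treatment effect. The change should be made before analysis.

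**What to change.** 1. Replace the raw tests with the planned RDD specification (threshold indicator plus Hb on each side), fitted within each sex with each baseline variable in turn as the outcome. Use the analysis range or a bandwidth stated in advance, and the same care over functional form as for the outcomes.
2. Report each estimated jump with its 95% CI, not only a p-value. Read a null result through the interval: it reassures only if it excludes imbalances that would matter.
3. Fix the adjustment set in advance, for example age, comorbidity and surgery type, identical for women and men, and drop the rule that admits covariates by significance.
4. Keep the histogram, the McCrary test and the covariate-adjusted sensitivity analyses.

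The cost is a few sentences in the SAP; data and code are those of the main RDD. The price is precision: about four times the variance of a raw mean difference in the same window. The check should therefore use a wider range than a narrow raw comparison would, which it can do without inflating false alarms provided that the Hb trend is adequately modelled.

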### Comparing ITS and RDD

Both ITS and RDD have significant advantages over the typical pre-post analysis often seen in medical literature. When an intervention is introduced rapidly and short-term outcomes are frequently assessed, ITS can be considered a sub-type of RDD in which the assignment variable is time and the cut-off occurs when the policy is introduced
^28^.

It is unusual to have a dataset amenable to both types of analysis; however, they provide different perspectives. Whilst both deigns share the strength of not being bound by the selective inclusion criteria of a RCT, thus potentially improving generalisability, they also have their limitations.

In the case of RDD, in order to ensure groups either side of the threshold are similar the focus is on an effect close to the threshold value. (i.e. female patients with Hb 119 or 121g/L are likely very similar, but those with Hb 90 or 140 are likely different in other, unmeasured parameters). This limits the generalisability of findings to values that lie far from the threshold. In the case of ITS the results can be impacted by several factors such as autocorrelation and unmeasured confounders, which we have attempted to address in the analysis design. Also, the findings from ITS can only indicate an associative not a causal relationship between intervention and outcomes, whereas RDD has the potential to demonstrate causation.

### Dissemination

Publication of study results will be sought in a high impact journal.

## Study status

Study data has been collected and analysis pending awaiting publication of this statistical analysis plan.

## Data availability

No data is associated with this article.
